## Abstract

**Background:**

Globally, 220 million women experience an unmet need for family planning. A newly designed female condom, the Woman’s Condom (WC), has been developed featuring an improved design. It is the first dual-protection, female-initiated contraceptive that is a premium, higher price point product. However, market availability alone will not increase uptake. In February 2016 the WC will be distributed with a strong media campaign and interpersonal communication (IPC) outreach intervention. The impact of these on knowledge, acceptability, and use of the WC will be measured.

**Methods/design:**

A baseline survey of 2314 randomly selected 18- to 24-year-old sexually active men and women has been conducted. The WC and mass media will be introduced throughout 40 urban wards in and surrounding Lusaka, Zambia. The baseline survey will serve as a quasi-control arm to determine the impact of introducing the WC with mass media. Half of the wards will be randomly allocated to additionally receive the IPC intervention. A single-blind randomized controlled trial will determine the impact of the IPC intervention on knowledge, uptake, and use of the WC. After one year, another 2314 individuals will be randomly selected to participate in the endline survey.

We hypothesize that (1) the distribution and media campaign of the WC will increase overall condom use in selected urban wards, and specifically use of the WC; (2) the IPC intervention will significantly impact knowledge, acceptability, and use of the WC.

The primary outcome measures are use of the WC, use of any condom, and willingness to use the WC. Secondary outcomes include measures of knowledge, acceptability, and choice of contraception.

Odds ratios will be estimated to measure the effect of the intervention on the outcomes with 95% confidence intervals. All analyses will be based on the intention-to-treat principle.

**Discussion:**

Increasing uptake of dual prevention measures (such as the WC) may reduce incidence of sexually transmitted infections/HIV and unplanned pregnancies. It is important to ensure young, urban adults have access to new contraceptive methods; and, understanding how mass media and IPC impact contraceptive knowledge, acceptability, and use is critical to reduce unmet need.

**Trial registration:**

AEARCTR-0000899. Registered on 26 October 2015.

**Electronic supplementary material:**

The online version of this article (doi:10.1186/s13063-016-1681-x) contains supplementary material, which is available to authorized users.

## Background

Globally, 220 million women experience an unmet need for family planning (FP) [1], and more than 100 million women cite method-related reasons for non-use of modern contraceptives [2]. There is a need to diversify the contraceptive choices for women who have different needs, particularly in developing countries, where women are at high risk for sexually transmitted infections (STIs) such as HIV and may lack control over sexual and reproductive decisions due to gender inequity [3]. The Expanding Effective Contraceptive Options (EECO) project was designed to support the research, development, and introduction of new contraceptive methods, with the goals of addressing method-related reasons for non-use, expanding contraceptive choice, and increasing access to woman-initiated methods in order to meet the reproductive health needs of women and girls worldwide. However, just having a product available does not mean it will be used; strategies to increase uptake are still necessary and often lack evidence.

Through the EECO project, a third generation, newly designed premium female condom (FC) called the *Woman’s Condom* (WC), developed by the Program for Appropriate Technology in Health (PATH), has been marketed in Zambia under the brand name *Maximum Diva Woman’s Condom* (WC) by the Society for Family Health (SFH), the Zambian subsidiary of Population Services International (PSI). Previous iterations of the FC, such as the Care Condom or FC2, have been underutilized. To date, FCs only represents 0.8% of the total condoms distributed by donor nations [3]. Attempts to introduce FCs worldwide have encountered barriers such as weak distribution channels within national health systems and critiques of the product design and marketing. The new WC product features an improved design and will be coupled with a multipronged marketing campaign that addresses some of these concerns. The marketing strategy is more streamlined, with a clearly defined target population. In piloting, the product has received positive feedback on its design and ease of use, and it will be marketed with a higher price point as a premium product in urban settings.

In addition to understanding the impact of the new WC on the condom market, it is also critical to develop a strategy to increase knowledge, acceptability, and uptake of the new WC. During the distribution of the WC and its mass media campaign, this randomized controlled trial (RCT) will measure the impact of a interpersonal communication (IPC) intervention. IPC interventions here are community based small groups led by trained IPC agents that will demonstrate proper WC use and promote conversations between sexual partners in condom negotiation to change contraceptive norms and product acceptability. To date, no rigorous evaluations of IPC interventions that aim to improve uptake of products have been conducted, particularly among a general population of young people. Recent research does suggest that exposure to IPC is associated with knowledge acquisition and acceptability of sensitive topics such as condom use [6]; however, there is a lack of causality.

This study will measure the impact of the new, premium WC on the condom market and how it impacts user contraceptive preferences and brand selection. This study will also implement an RCT designed to measure the added impact of a community-based IPC intervention on improving WC (and overall condom) knowledge, acceptability, and use, as compared with a mass media campaign only.

### Objectives and hypothesis

The overall objective of this RCT is to evaluate how the introduction of the WC impacts the condom market in Zambia. Specifically, we will evaluate the effectiveness of IPC plus mass media plus distribution of WC (intervention) compared to mass media plus distribution of WC (control) on the prevalence of WC use and prevalence of overall condom use. The conceptual framework is described in Fig. 1.

**Fig. 1 Fig1:**
[figure not shown]
Summary of conceptual framework

The primary objectives of this evaluation are:To assess the effect of the introduction of the WC on the overall condom market (self-reported condom use and self-reported use of WC)To determine the additional effect of an IPC intervention on self-reported *use of the WC* as compared with just mass media including a website (controlling for any differences between the intervention and control groups)To determine the additional effect of an IPC intervention on self-reported *use of any condom* as compared with just mass media including a website (controlling for any differences between the intervention and control groups)To determine the additional effect of an IPC intervention on *willingness to use an FC* (and specifically, the WC) as compared with just mass media including a website (controlling for any differences between the intervention and control groups)

The secondary objectives of this evaluation are:5.To determine the effect of an IPC intervention on self-reported *knowledge, attitudes, and practices regarding the FC, specifically the WC*, as compared with just mass media including a website (controlling for any differences between the intervention and control groups)6.To determine the effect of an IPC intervention on community-level *acceptability of an FC, specifically the WC*, compared with just mass media including a website (controlling for any differences between the intervention and control groups)7.To determine the effect of an IPC intervention on self-reported *changes in interpersonal communication with sexual partners* regarding contraceptive use as compared with just mass media including a website (controlling for any differences between the intervention and control groups)8.To assess women’s and men’s preferences for condom brands.

## Methods/design

The overall aim of this study is to assess the impact of introducing the WC on the overall condom market. We will also evaluate the effectiveness of IPC plus mass media plus distribution of WC (intervention) compared with mass media plus distribution of WC (control) on the self-reported prevalence of WC use and prevalence of overall condom use using an RCT design. Forty urban wards in Lusaka and nearby districts (Chilanga, Kafue, and Chongwe) will be randomized to the control or intervention arm with a 1:1 allocation ratio. The baseline survey conducted in all 40 wards will be analyzed as a quasi-control arm in order to assess the effect of the introduction of the WC on the total condom market. This will be done for two reasons: (1) there are no comparably urban areas in the country to act as control settings; (2) the potential for spillover for a new condom product and its marketing campaign is extremely high, making a true control arm logistically and technically impossible. The media campaign will be displayed on a website and billboards throughout the city; thus these cannot be geographically limited.

When the baseline survey is implemented, no WC will be available, as is the status quo in Lusaka. After rollout of the WC, wards in the control arm will receive only the WC and a mass media campaign. Intervention wards will receive the WC, a mass media campaign, and the IPC intervention. The RCT component of this study will aim to evaluate the added impact of the IPC intervention compared with just distribution of the WC and the mass media campaign. The trial will be evaluated through baseline and endline questionnaires administered to eligible individuals residing within randomly selected households located in these wards. The Standard Protocol Items: Recommendations for Interventional Trials (SPIRIT) checklist was used to prepare the study protocol (Additional file 1). The resulting protocol schedule of procedures and activities for this study is outlined in Table 1 as per the SPIRIT guidelines.

**Table 1 Tab1:** SPIRIT protocol schedule of procedures and activities for Maximum Diva study

	Study period					
	Prep. phase	Baseline survey	Randomization	Intervention period	Endline survey	Close-out
Activity	*-t* _*1*_	0		*t* _*1*_	*t2*	*t3*
Enrollment:						
Sampling and mapping	X					
Informed consent written	X					
Hiring and training surveyors	X					
Piloting, revising survey tool	X					
Interventions:						
Randomization			X			
Distribution plus mass media (control)				X		
IPC (intervention)				X		
Assessments:						
Baseline survey		X				
Baseline outcomes of interest: male condom use in last 6 months, male condom use at last sexual intercourse, types of contraception used, interest in using female condom in the future		X				
Endline survey					X	
Endline outcomes of interest: WC use (last 6 months, last sexual intercourse), attended IPC, knowledge of WC, interest in using WC					X	
Dissemination:						
Write up manuscripts for peer-reviewed publication, present at relevant international and local conferences, host dissemination event with local stakeholders						X

### Setting and participants

The new WC product is being distributed in urban wards that comprise Lusaka, the capital of Zambia (see map of selected wards; Fig. 2). A baseline survey was conducted in November 2015, and an endline survey will be conducted in March 2017, each sampling from randomly selected households within 40 selected urban wards. One individual per household will be enrolled and administered the questionnaire if the person has lived in the house for at least the past 6 months (to ensure exposure to the WC and the IPC intervention in the intervention wards), is between the ages of 18 and 24 years, and is sexually active (has had sex in the last 6 months) (eligibility criteria). Both men and women will be included in the study.

**Fig. 2 Fig2:**
[figure not shown]
Map of selected wards in Zambia, and sampling methodology (example: Matero ward)

### Intervention

The WC program comprises three components: (1) distribution of the WC, (2) a mass media campaign, and (3) an IPC intervention. These are defined as follows:Distribution of the WC: The WC will be distributed to pharmacies and other outlets such as chemists and stores by the SFH located in the geographic areas where the study will be implemented. The distribution of the WC will take place across both study arms. Information regarding where the WC is stocked and how often it is available will be collected throughout the study to determine availability of the product and whether that varies across wards.Mass media campaign: The WC will be advertised widely, targeting young adults through radio, billboards, news media, social media, and a mobile website. The mobile website and accompanying media will be branded under the “Smart Choices” campaign (SmartChoices.co.zm). The website will serve as a main venue for the introduction and promotion of the WC. The media campaign in its various forms will disseminate information about family planning and serve as an interactive forum for young men and women to ask sexual health related questions and generally discuss SRH related topics. SMS blasts and social media messaging will be used to direct individuals to the website.Interpersonal communication (IPC): IPC agents will be recruited from wards within the intervention arm. They will be paid and trained by the SFH on communication skills, sexual and reproductive health information, technical specifications and use of the WC, and condom negotiation skills with sex partners. IPC agents will set up an IPC point in a high traffic area(s) of each ward selected for the intervention arm for initial demand creation, and will use their existing and new contacts to access networks of young people in the area for smaller group and one-on-one information sessions. The IPC intervention will comprise communication messages focused on how to use and the benefits of the use of WCs and male condoms for the prevention of unplanned pregnancies. IPC activities will be targeted to both young men and women (aged 18–24 years). The IPC agents will also be young (18–35 years of age) males and females. The key components of the IPC intervention include (1) targeting men and women aged 18–24 years, (2) providing content on the importance of contraceptive use with a focus on the benefits of FCs, (3) demonstrating how to use the WC on a pelvic model, and (4) training on condom use negotiations with a sex partner through theater or role playing. Information will also be distributed in the form of pamphlets, and tools used for the IPC sessions will include flip charts and tablets.

### Sample size

To calculate the sample size needed in each trial arm, we considered prevalence of any condom use (percentage) as our outcome of interest. The contraceptive prevalence rate (CPR) for any modern contraceptive method in urban Zambia (for 15- to 49-year-old married women) is currently about 53% [4]. However, our study includes both married and unmarried women. A report from 2009 by the Zambian Statistics Office reported urban condom use to be 54% in Zambia [7]. We used 53% to calculate our sample size, and aim to detect a minimum increase of 5% use with 80% power at the 95% significance level. Because the trial is clustered at the ward level (with many individuals living within a ward), the sample size needs to be increased to account for intraclass correlation (ICC) within wards. However, no information was found from previous studies on the likely between- or within-cluster correlations in FC use in previous cluster-randomized trials. When the ICC cannot be estimated, common practice is to double the sample size to account for clustering.

Using Stata (StataCorp, College Station, TX, USA), we calculated the sample size required to detect a 4%, 5%, and 7% increase in any use from a 53% baseline use and an estimated standard deviation (SD) of 0.15, doubling the sample size to account for the unknown ICC. Lastly, we added 10% to increase the sample size to account for potential refusals. We will use a sample size of 1157 individuals per arm (a total of 2314 individuals in both arms). This yields a total of 58 individuals to be interviewed per ward, in a total of 40 wards (see Table 2).

**Table 2 Tab2:** Sample size required to detect a 2, 3, and 4 percentage point increase in condom use (4%, 5%, and 7% increase)

Hypothesized standard deviation of condom use	Hypothesized increase in proportion of condom use between groups	Sample size required in each group (ratio 1:1)	Adjusted for effect of clustering (design effect = 2)	10% refusal rate (estimated)
0.15	7%	296	592	651
0.15	5%	526	1052	1157
0.15	4%	1183	2366	2603

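### The text states 80% power, but every row of Table 2 reproduces only at 90%, and two of its three percent labels are misrounded

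*Protocol article*

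**What the plan says.** The Sample size section of the protocol article takes a proportion as the sizing outcome ("we considered prevalence of any condom use (percentage) as our outcome of interest") and fixes the baseline: "We used 53% to calculate our sample size". The aim is to "aim to detect a minimum increase of 5% use with 80% power at the 95% significance level". The calculation uses "an estimated standard deviation (SD) of 0.15, doubling the sample size to account for the unknown ICC", and then adds 10% for refusals.

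Table 2 is captioned "Sample size required to detect a 2, 3, and 4 percentage point increase in condom use (4%, 5%, and 7% increase"). For increases labelled 7%, 5% and 4%, it gives 296, 526 and 1183 per group before inflation. These become 592, 1052 and 2366 after a design effect of 2, and 651, 1157 and 2603 after the 10%. The 5% row is adopted: 1157 per arm, 2314 in total, 58 per ward in 40 wards.

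**The concern.** The text and the table should describe one calculation. The text gives 80% power; the table should then follow from 80%, the stated SD and the stated differences. It does not.

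The target effect is also hard to read. The running text and the table column give 5% without saying that it is relative. Only the caption links it to 3 percentage points, and that link is not exact on a 53% baseline.

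The adopted row fixes the size of the trial. Any condom use is a primary outcome, and a null result on it is read against the difference and power the trial was planned for. As printed, a reader cannot state both with confidence.

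**Working it through.** **Inputs (Sample size section and Table 2):** SD 0.15; baseline 53%; differences d of 4, 3 and 2 points (caption); 1:1 allocation; design effect 2; refusals as × 1.10. The "with 80% power at the 95% significance level" is taken as alpha 0.05. Sidedness is not stated; two-sided is assumed and one-sided was also tried.

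**Formula per group:** n = 2 × (z_alpha + z_power)² × SD² / d², rounded up, then × 2 × 1.10.

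**Reproducing the table at 90% power**, two-sided: (1.960 + 1.282)² = 10.507, and 2 × 10.507 × 0.0225 = 0.4728.
- d = 0.04: 295.5, so 296, then 592, then 651
- d = 0.03: 525.4, so 526, then 1052, then 1157
- d = 0.02: 1182.1, so 1183, then 2366, then 2603

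All nine sample-size cells match.

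**At the stated 80% power**, two-sided: (1.960 + 0.842)² = 7.849, and 2 × 7.849 × 0.0225 = 0.3532.
- d = 0.04: 221, then 442, then 486
- d = 0.03: 393, then 786, then 865
- d = 0.02: 883, then 1766, then 1943

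No cell matches. One-sided 5% does not match either: 174, 310 and 696 at 80%; 241, 429 and 964 at 90%.

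**Percent labels on a 53% baseline:** 2/53 = 3.8%, correctly rounded to 4%. 3/53 = 5.7%, printed as 5%. 4/53 = 7.5%, printed as 7%.

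**Literal 5% relative increase:** 0.05 × 53 = 2.65 points. At 80% power, 0.3532 / 0.0265² = 503, then 1006, then 1107. The planned 526 per group gives 81.7% power for 2.65 points. On the same reading the 7% row (3.71 points) needs 257 and the 4% row (2.12 points) needs 786, against 296 and 1183 printed.

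**Binary variance, for the restatement:** the SD of a yes/no outcome at 53% is √(0.53 × 0.47) = 0.499, not 0.15. After the design effect and refusals, 1157 per arm corresponds to 1157 / (1.10 × 2) ≈ 526 effective per arm. For 53% against 56%:

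z = (0.03 × √526 − 1.960 × √(2 × 0.545 × 0.455)) / √(0.53 × 0.47 + 0.56 × 0.44) = (0.688 − 1.380) / 0.704 = −0.98, a power of about 16%.

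If all 1157 are interviewed (578.5 effective), power is about 17%. The difference detectable at 80% power with 526 effective per arm is about 8.5 points.

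**The case against.** The best defence is that the stated aim is met. Read literally as a relative increase, 5% of 53% is 2.65 points, and 526 per group has about 82% power for that on the protocol's SD. Working backwards, 526 per group at 80% detects 2.80 × 0.15 × √(2/526) = 2.59 points, or 4.9% relative, and 296 detects 6.5%, which could be rounded to 7%. This much stands: it would be wrong to say that 1157 fits the stated aim on no reading. It does not explain the table, however. The same calculation for 1183 gives 3.3%, not 4%. This reading also returns none of the printed counts, whereas 90% power returns all of them.

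A second defence is that the caption ties 5% to 3 points. That also stands. A reader of the running text alone might infer a 5-point target, for which SD 0.15 and 80% power need only 142 per group (about 312 after inflation). The caption rules this out, so it is not the document's own reading. The labels are loose rounding, not a second contradiction.

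Third, the mismatch does no harm by itself. On SD 0.15, 1157 per arm exceeds the 865 needed for 3 points or the 1107 needed for 2.65 points at 80%. A reader might infer that the power error leaves the trial too small; it does not. Any shortfall comes from the SD, which is a different fault.

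**Conclusion.** The stated power and Table 2 contradict each other. The table matches 90% power in every cell; the text says 80%. The 90% is inferred from the arithmetic, assuming a two-sided 5% test, and is stated nowhere. An exact match on three rows makes the inference strong, but the documents do not show which of the two figures was intended.

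For the adopted row the gap is 526 against 393 per group, about 34% (526/393 = 1.34), or 1157 against 865 per arm. It is conservative on the protocol's SD. Two of the three percent labels are misrounded, and 5% is not marked as relative where it is used.

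This is a wrong figure in the paragraph that justifies the trial's size, and it should be corrected. It is not in itself evidence of an underpowered trial. The 16% power and 8.5-point figures rest on the binary variance and the protocol's assumed design effect of 2. They belong to the separate question of the SD and are given here because a restatement that left out the correct variance would be wrong again.

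**What to change.** Keep 1157 per arm. In the Sample size section, state one target difference in percentage points, one power, and a two-sided 5% significance level. Make Table 2 follow from them. Head the effect column in percentage points; if relative figures are kept, mark them as relative and print 3.8%, 5.7% and 7.5%.

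Use the binary variance at 53% in the restatement. Report what the planned size delivers with the assumed design effect: about 16% power for 3 points, or about 8.5 points detectable at 80% with 526 effective per arm. The remedy is to restate what 1157 can show, not to enlarge the sample.

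The cost is one paragraph and one table, with no change to fieldwork. The restated power will be far lower than the article now implies.

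### The sample size gives a yes/no outcome at 53% an SD of 0.15, so the claimed 80% power for a 5% rise in any condom use is about 15% to 18%

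*Protocol article*

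**What the plan says.** The protocol article, under Sample size, names its sizing outcome: "we considered prevalence of any condom use (percentage) as our outcome of interest". The baseline value is explicit: "We used 53% to calculate our sample size". The target is to "aim to detect a minimum increase of 5% use with 80% power at the 95% significance level". The calculation then sets out to "detect a 4%, 5%, and 7% increase in any use from a 53% baseline use and an estimated standard deviation (SD) of 0.15". The result is doubled because the ICC is unknown, and 10% is added for refusals. No source is given for the 0.15.

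The title of Table 2 equates relative increases of 4%, 5% and 7% with 2, 3 and 4 percentage points. Its row for 5% runs 526, then 1052 with design effect 2, then 1157 per arm. The total is 2314, or 58 per ward in 40 wards. Under Primary and secondary outcomes, any condom use (ever, in the past 6 months, at most recent intercourse) is one of three groups of primary outcomes.

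**The concern.** Each respondent either used a condom or did not. For such an outcome the SD is not a separate quantity to be estimated, because the prevalence fixes it. At 53% it is close to its maximum of 0.5. An SD of 0.15 would suit a continuous measurement or a set of ward percentages, but Table 2 uses it to count individuals.

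At stake is the stated power for the comparison on which the trial was sized: wards with and without interpersonal communication (IPC), on any condom use. If the SD is wrong by this much, the protocol promises a sensitivity to small effects that the design does not have.

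**Working it through.** **Inputs, all from Sample size and Table 2.** Control proportion 0.53; SD 0.15; increases of 4, 3 and 2 points; design effect 2; 10% added; 1157 per arm; 20 wards per arm. A 5% level is stated without sidedness. Two-sided is assumed, and it matches the table.

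**Step 1: reproduce Table 2.** For two means, n per arm = 2 x (SD/d)^2 x (z_alpha + z_beta)^2. The last factor is 7.849 at 80% power and 10.507 at 90%.

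| Difference d | n at 80% | n at 90% | Table 2 |
|---|---|---|---|
| 0.04 | 221 | 296 | 296 |
| 0.03 | 393 | 526 | 526 |
| 0.02 | 883 | 1183 | 1183 |

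All three rows match at 90% power and none at 80%. Taking 5% as exactly 2.65 points gives 503 at 80%, which is not 526 either. The remaining steps follow: 526 x 2 = 1052, and 1052 x 1.1 = 1157. So 0.15 was used as an individual-level SD in a two-means formula, at a power other than the one stated.

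**Step 2: the SD of the outcome.** sqrt(0.53 x 0.47) = 0.499. The variance ratio is 0.2491/0.0225 = 11.1.

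**Step 3: required numbers for two proportions.** n = [1.960 x sqrt(2 x pbar x (1 - pbar)) + 0.842 x sqrt(p1(1 - p1) + p2(1 - p2))]^2 / (p2 - p1)^2. For 0.53 against 0.56, pbar = 0.545 and n = (1.960 x 0.7042 + 0.842 x 0.7039)^2 / 0.0009 = 4324 per arm. With design effect 2 this is 8648. Table 2 has 526 and 1052, so the shortfall is a factor of 4324/526 = 8.2.

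**Step 4: power of the planned size.** The effective number per arm is 1157/2 = 578.5, or 1052/2 = 526 if 10% are lost to refusal. For 53% to 56% with 578.5, the critical difference is 1.960 x sqrt(0.49595/578.5) = 0.0574 and the standard error under the alternative is sqrt(0.4955/578.5) = 0.0293. Power is the normal probability below (0.0300 - 0.0574)/0.0293 = -0.94, which is 17.5%. The other cases follow in the same way:

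| Rise from 53% | 1157 per arm | 1052 per arm |
|---|---|---|
| 2.65 points (exact 5% relative) | 14.6% | 13.6% |
| 3 points (Table 2 title) | 17.5% | 16.3% |
| 5 points | 40% | 37% |

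**Step 5: detectable difference.** Solving for 80% power gives 8.1 points with 1157 per arm and 8.5 with 1052. A design effect of 2 at 57.85 respondents per ward implies an ICC of 1/56.85 = 0.0176. The documents give no ICC. For assumed values of 0.01 and 0.05, the detectable difference with 1157 per arm is 7.2 and 11.2 points.

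**The case against.** Four defences can be offered for the power claim, and none restores it.

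- *5% means percentage points.* The Table 2 title says 3 points, and a 5-point rise still has only 40% power.
- *The design effect is too harsh.* With no clustering at all, 3 points has 30% power.
- *0.15 is the between-ward SD of ward prevalence.* Then 526 would count wards. The implied ICC would be 0.0225/0.2491 = 0.09, which contradicts a design effect of 2, and 20 wards per arm would have about 9% power for 3 points.
- *Stratified randomization and covariate adjustment add precision.* They may. The gain cannot be quantified from the article, and it would not plausibly lift 15% to 18% to 80%.

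Some objections do stand, and they limit what may be inferred.

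- A reader might conclude that every figure in Table 2 is 11 times too small. Eleven is the variance ratio, and it carries over to sample size only at the 90% power the table used. At the stated 80% the factor is about 8.
- A reader might conclude that the trial cannot see effects below 8 points. Eight points is where power reaches 80%, not a floor: at design effect 2, power is 54% for 6 points and 67% for 7.
- A reader might expect a null result to be reported as excluding a 3-point effect. Nothing in the article says so, and Statistical methods already commits to odds ratios with 95% confidence intervals.
- The doubling is not itself an error. The article says openly that no ICC was found and then adopts a fallback: "When the ICC cannot be estimated, common practice is to double the sample size to account for clustering". The baseline survey was sized by this calculation, so its data could not have informed it.

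**Conclusion.** The point holds. The protocol states 80% power to detect a 5% increase in any condom use. On its own prevalence, design effect and numbers, power is about 15% (2.65 points) to 18% (3 points), or about 14% to 16% if only 1052 per arm are analysed. The cause is the SD of 0.15, confirmed by the exact match of all three table rows. The same match shows a second inconsistency: the table was computed at 90% power while the text says 80%. This does not help, since the requirement for a binary outcome far exceeds the plan at either level.

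These figures rest on a two-sided 5% test, a design effect of 2, and no gain from stratification or adjustment. One-sided power with 1157 per arm would be 23% to 27%. The conclusion is confined to any condom use. A reader might extend it to use of the Woman's Condom or willingness to use it, but the article gives no sizing inputs for those outcomes and nothing here bears on their power.

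**What to change.** Keep the 2314 respondents and correct the statement before the endline survey, which Trial status describes as still being planned.

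1. Delete the claim of 80% power for a 5% increase.
2. Recalculate Table 2 with the two-proportion formula, at one power stated identically in text and table, with 20 wards per arm. Express increases in percentage points.
3. Take the prevalence and the ward-level ICC of condom use from the completed baseline survey in the same 40 wards, in place of 53% and the doubling rule.
4. State the detectable difference that results. With the present inputs it is about 8 percentage points at 80% power. Say that smaller effects would be detected with lower power.

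The cost is one calculation on data already held and a rewritten paragraph and table. No fieldwork changes. The price is a less favourable stated detectable effect.
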